**Expedited notification of serious and unexpected adverse reactions**

The investigator will notify the Sponsor of all suspected serious and unexpected adverse reactions (SARGI), who will be responsible for reporting them in accordance with current regulations on clinical trials to the AEMPS (and authorities of the Autonomous Communities, if

applicable) within a maximum period of 15 calendar days from the time they become known. When the SARGI has resulted in the patient's death or endangered their life, the notification will be made within a maximum period of seven calendar days from the time it becomes known. Subsequent event-related information will be provided within eight days.

#### d) Pregnancy

As the study includes individuals over 40 years of age, there is a possibility of pregnancy during the follow-up period. However, due to the naturalistic conditions of the study, it is not deemed necessary to enforce contraceptive measures for women of childbearing age (which could additionally introduce added risks). While the ADAMPA protocol does not assign drugs (and therefore there are no risks of adverse events associated with drug treatments derived from the study, as any such risks would arise from drugs prescribed by physicians independent of the study), pregnancy can complicate the management of hypertension (and vice versa) and necessitate specific and distinct monitoring beyond that outlined in the intervention protocol. Consequently, should a pregnancy occur during the follow-up period, affected women will be excluded from the assigned protocol and will be managed freely by their doctor(s), while maintaining endpoint follow-up and inclusion in the intention-to-treat analysis.

No additional explorations, tests, or complementary evaluations will be conducted beyond those undertaken in routine clinical practice.

#### e) Periodic safety report

During the study, the Unit responsible for Pharmacovigilance will prepare annual safety reports in line with recommendations from the ICH E2F guide. These reports will be presented to regulatory authorities and the CEIm following the established calendar in current legislation.

### **11. Statistical analysis**

#### **11.1 Sample size**

A sample size of 382 patients was estimated in order to have 90% power to detect a 5 mmHg (SD 15 mmHg) difference in SBP between groups (primary outcome) with a two-tailed contrast and an alpha error of 0.05. This figure represents a clinically relevant difference based on previous trials. We increased this figure to 458 participants (20% increase) to account for possible dropouts and loss to follow-up.

#### **11.2 Statistical analysis**

Analysis will be on an intention-to-treat basis for complete cases. We will use mixed models (general linear modeling –GLM) to compare SBP at 12 months between the intervention and control groups. This analysis will be presented in both crude and adjusted forms for the different covariates of interest (baseline BP, gender, GP/PCC-random effect, diabetes, etc.). A sensitivity analysis will be performed to examine the potential effect of missing data, which will include substitution by multiple imputation, replacement of data lost by the most recent data or by the mean of the series. Additionally, analyses of the main outcome measure by subgroups of age, gender, comorbidity, level of chronicity, better control at baseline, etc. will be performed.

Differences in secondary outcome measures (DBP, percentage of patients controlled, PDC, persistence and TI) will be analyzed using methods similar to those used for analysis of the main outcome measure.

### Economic analysis

The economic analysis will include a cost-consequence analysis, estimating both the costs (hospitalizations, outpatient visits, emergency visits and antihypertensive drugs) and the potential benefits (e.g. reduced incidence of stroke, myocardial infarction, etc.) in natural units. In addition, we will collect information on Health-Related Quality of Life (HRQOL) through the EQ-5d questionnaire, which will allow us to obtain utilities and therefore perform a cost-utility analysis with the estimated benefits in terms of Quality-Adjusted Life-Years (QALY).

A modeling will be performed to obtain longer-term predictions of the results observed in the trial. The results on which this modeling will be based will be survival, quality of life and costs associated with clinical events. A sensitivity analysis (deterministic and probabilistic) will be performed to analyze the robustness of the results. Key parameters will be modified to determine their impact on results. All analyses will be performed using STATA version 14.

### Quality Sub-study

Qualitative research techniques will seek to provide an in-depth understanding of the positive elements and areas of improvement related to self-titration and self-monitoring intervention. To this end, two meetings will be held, one with professionals (GPs and nurses) and one with patients, using the Nominal Group Technique (NGT). The NGT is a working methodology that establishes a framework for highly structured interaction that enables participation and equal consideration of the contributions of all members of the working group, and allows the identification of priorities, consensus and disagreement, solution generation and decision-making in an agile and objective manner (24).

## **12. ETHICAL ASPECTS**

### **12.1 Ethics Committee (Helsinki) and Authorities**

The investigator must conduct the study in accordance with the principles of the Declaration of Helsinki, the Good Clinical Practice (GCP) standards, as described in the Harmonized Tripartite Guide to Good Clinical Practice (International Conference on Harmonization, ICH, 1996). and Royal Decree 1090/2015, of December 4, which regulates clinical trials with drugs, the Ethics Committees for Research with drugs and the Spanish Registry of Clinical Studies.

The study protocol and its attached documentation will be sent for approval to the clinical research ethics committee (CEIC-HCUV) as well as to the Spanish Agency for Medicines and Health Products (AEMPS).

### **12.2 Informed consent**

Participant informed consent (IC) will be mandatory for study inclusion. The IC will be presented to participants during the selection session by the MEFI. This document will detail the trial's nature, patient implications for participating, protocol conditions, and potential risks associated with participation. The IC will include agreement to participate and permission to access clinical history for information on medication, medical history, clinical outcomes, and resource utilization. Participants will retain the right to leave the study at any time without compromising future healthcare.

Participants will have ample time to review information, consult the MEFI or relevant individuals, and make an informed decision. The written IC will include participant signature

and date, as well as date and signature of the person obtaining consent. The original IC will be kept in the investigator's file, with copies given to the patient and the MIC team.

### **12.3 Data protection**

Strict compliance with Law 15/1999 of December 13 on the Protection of Personal Data and its associated regulations is guaranteed.

Confidentiality of each patient's data will be maintained at all times. The original data will be retained at the health center and may only be accessed by study researchers, individuals responsible for monitoring, the Clinical Research Ethics Committee, and Spanish Health Authorities in case of inspection. Data used in the study will be identified by a code. The researcher is the only individual authorized to and responsible for knowing the source of the collected data and connecting them to the respective patient.

The main researchers and collaborators participating in the study, when handling patient data, will take appropriate measures to safeguard the data and prevent unauthorized third-party access.

### **12.4 Monitoring and auditing**

Platform for Clinical Research Units and Clinical Trials Spanish Clinical Research Network (SCReN) will monitor the study.

During the study, the monitor will visit the participating centers to verify that the patient documents are complete, that the data entry in the Data Collection Notebook (CRD) is accurate, that the study protocol and the standards of Good Clinical Practice and that progress in recruitment is correct.

The study principal investigator and collaborators should be available to assist the monitor during these visits.

The investigator must keep all the source documentation of each patient included in the study (hospital medical records, including medical and demographic information and the results of any other test or evaluation). All the information that is registered in the Data Collection Notebook (CRD) must be verifiable with the source documents of the patient's file. The investigator must retain the original informed consent signed by the patient (a signed copy will be provided to the patient).

Monitoring will require full verification of the existence of informed consent, of compliance with the inclusion/exclusion criteria, and of the data to be used for all primary endpoints.

Additional checks will be carried out to verify that the source data matches the data in the Data Collection Notebook (CRD) according to the study monitoring plan.

The ICH Harmonized Tripartite Standards for Good Clinical Practice state that research sites and all data, including source data, should be available for inspection by competent authorities. The Patient Information Sheet (HIP) will inform patients that their medical records may be reviewed during these audits.

### **12.5 Protocol Compliance.**

This protocol defines the objectives and procedures of the study and the data to be collected from study participants. An investigator may not, under any circumstances, collect additional data or carry out any other procedure for any other purpose not described in the study protocol.

Investigators must exercise caution to prevent deviations from the protocol. If an investigator believes that a deviation would enhance the study's execution, it must be regarded as an amendment to the protocol. This amendment cannot be implemented until approved by the study investigators, the Clinical Research Ethics Committee (CEIm), and, when necessary, the Spanish Agency of Medicines and Medical Devices (AEMPS).

### **12.6 Early Termination or Suspension of the Study**

The study will be interrupted when statistically significant differences are observed in the presence of serious adverse events related to the intervention.

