### **6.7 Study discontinuation criteria**

Based on the study's characteristics and considering previous experiences, there is no anticipation of needing to interrupt the study due to safety concerns or lack of efficacy. Consequently, there will be no interim analysis conducted for these purposes, nor is the presence of a dedicated safety committee required. If any serious adverse events do arise, the trial research team will be responsible for their evaluation.

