## 10. SAFETY ASSESSMENT

The ADAMPA study is a clinical trial carried out under naturalistic conditions where the intervention is based on self-monitoring and self-adjustment of medication in poorly controlled hypertensive patients. The antihypertensive drugs used will be those that patients are taking as part of their usual medication. It is considered a low-risk clinical trial, and no differences in adverse events are expected compared to usual medical practice. Therefore, the need for a safety committee has not been anticipated. The reference safety information will be the technical data sheets of each of the antihypertensive drugs. Consequently, it is the investigator's responsibility to detect and document any event that meets the criteria and definitions of adverse events (AE) or serious adverse events (SAE), especially when such events are not described in the technical sheet.

During the study, the existence of adverse events, whether serious or not, will be checked according to the definitions provided in this section of the protocol. The Sponsor will be responsible for promptly notifying Health Authorities, such as the Spanish Agency for Medicines and Health Products (AEMPS), and Autonomous Communities (CCAA) if applicable, about serious and unexpected adverse reactions (RAGI), annual reports, or any other relevant

safety information. Additionally, the Sponsor will be responsible for notifying researchers about safety information.

a) Definitions:

**Adverse event (AE)** Refers to any harmful incident to a patient or clinical trial subject treated with a drug, even if it doesn't necessarily have a causal relationship with the treatment.

**Adverse reaction (AR):** Denotes any harmful and unintentional reaction to an investigational drug, regardless of the administered dose.

**Serious adverse event (SAE):** Encompasses adverse events that, at any dose, cause death, threaten the subject's life, require hospitalization or its prolongation, result in permanent or significant disability, disability, or give rise to a congenital anomaly or malformation. For notification purposes, suspected adverse events considered important from a medical perspective will also be treated as serious, even if they don't fully meet the above criteria.

**Serious and Unexpected Adverse Reaction (GUAR):** Represents an adverse reaction whose nature or severity doesn't correspond to the information in the product's technical data sheet.

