**Serious adverse events that do not require immediate notification by the investigator**

The following serious adverse events do not require immediate notification by form:

- Thromboembolic events (deep vein thrombosis, pulmonary thromboembolism)
- Neurological events (stroke, cerebrovascular accident, acute confusional syndrome)
- Cardiological events (angina, myocardial infarction, cardiac arrhythmia, decompensation of heart failure, hypotensive crises)
- Impaired renal function
- Gastrointestinal bleeding
- Need for blood transfusion
- Hospitalization due to hydroelectrolyte disorder

In any case, there will be a section in the CRD to collect information on possible serious adverse events reported by the patient during follow-up visits. Serious adverse events that do not require immediate notification must be included in the clinical history and in the CRD, and will be included in the periodic safety report.

On the other hand, the study will collect data related to urgent hospital admissions due to episodes of angina, myocardial infarction, stroke, and hypotensive crises, as well as death from any cause, along with outpatient and emergency visits due to hypotensive crises, as part of the tertiary objectives of the study. Given the characteristics of the included population (and the results of the TASMINE-SR^17 study), figures of less than 3% are expected for the combined endpoints; therefore, it is not anticipated that differences will be detectable. For these serious events, as well as for deaths, the Family Physician Investigators responsible for the patients (MEFI) will review the medical history and determine their potential relationship with the intervention. Previous trials have failed to find any evidence of such a relationship.

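### Section 12.6 stops the trial on a significant between-arm difference in SAEs, section 6.7 says no such interim analysis will be made, and the events to be compared are not defined

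*Protocol*

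**What the plan says.** Section 12.6 of the protocol, the only section on early termination, consists of one sentence: "The study will be interrupted when statistically significant differences are observed in the presence of serious adverse events related to the intervention." It is worded as an obligation.

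Section 6.7 says that "there is no anticipation of needing to interrupt the study due to safety concerns or lack of efficacy". It continues: "Consequently, there will be no interim analysis conducted for these purposes, nor is the presence of a dedicated safety committee required." If serious adverse events arise, "the trial research team will be responsible for their evaluation". Section 10 repeats that "the need for a safety committee has not been anticipated".

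Relatedness is described in two ways:

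- The causality criteria in section 10, and section 4 of the SAE form in Annex 1, assess it against a drug.
- For the listed cardiovascular events and deaths, section 10 instead says that the family physician investigators (MEFI) "will review the medical history and determine their potential relationship with the intervention".

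For the combined clinical endpoints collected as tertiary outcomes, section 10 expects that "figures of less than 3% are expected for the combined endpoints; therefore, it is not anticipated that differences will be detectable".

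**The concern.** A statistically significant difference can be observed during the trial only if someone counts events by arm and tests them while data accumulate. That is an interim safety analysis, and section 6.7 says none will be made. A reader of 12.6, including an ethics committee, would take it for a working safeguard. A reader of 6.7 would conclude that the comparison it depends on never takes place.

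The quantity to be tested is a second difficulty. If relatedness is to the drug, events can arise in both arms. If it is to self-monitoring and self-titration, controls have almost nothing to relate an event to, and the between-arm test shrinks to a count in one arm. That count would be attributed by physicians who are not masked (6.3.2) and who set the self-adjustment plan themselves (8.5.1).

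There are two things at stake. The stopping rule may never be applied. Or someone may run an unplanned, unmasked comparison on an undefined endpoint and stop the trial before the 12-month primary analysis.

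**Working it through.** **1. The passages side by side.**

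| Question | Section 12.6 | Elsewhere in the protocol |
|---|---|---|
| Is there a between-arm test during the trial? | Implied; the rule cannot operate without it | 6.7: no interim analysis for safety or lack of efficacy |
| Who makes it? | Not stated | 6.7: research team evaluates SAEs; 6.7 and 10: no dedicated committee planned |
| When? | Not stated | 10(e): annual safety reports, no comparison by arm described |
| On which events? | SAEs related to the intervention | 10 and Annex 1: relation to the drug; 10, for listed events and deaths: relation to the intervention, judged by the MEFI |

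A statistical analysis plan could supply a test and a level. It could not make 12.6 agree with a protocol statement that the analysis will not be done.

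**2. Inputs.** Section 12.6 gives no figure to reproduce. The arm size comes from section 11.1 and Table 1. A two-sample t-test for 5 mmHg, SD 15, two-sided 0.05 and 90% power gives 191 per arm, 382 in total (power 0.901). Then 382 × 1.2 = 458.4, stated as 458, or 229 per arm. The plan's figures reproduce. Section 10 supplies the figure of under 3%, for the combined endpoints only. The two-sided 5% level, Fisher's exact test and every other event rate below are assumptions.

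**3. Reading A: relation to self-monitoring and self-titration, control count 0.** With equal arms and no control events, the two-sided Fisher p-value for k events is 2 × C(229,k) / C(458,k).

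- k = 5: p = 0.061
- k = 6: p = 0.030

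The rule therefore becomes six attributed events in the intervention arm, or 6/229 = 2.6%. The chance of six or more by the end of the trial is 3%, 31% and 69% at assumed true rates of 1%, 2% and 3%.

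**4. Reading B: events possible in both arms.** At 3%, 0.03 × 229 = 6.87, so take 7 control events.

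- 17 v 7: p = 0.057
- 18 v 7: p = 0.038

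Eighteen events are 18/229 = 7.9%, about 2.6 times the control count. Exact power of the Fisher test for an assumed 3% v 6% is 0.267, about 27%; the normal approximation gives 34%.

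**5. Comparison.** The same sentence in 12.6 needs 6 events on one reading and 18 on the other. The document does not say which is meant.

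**The case against.** The strongest reply is that the trial does have safety oversight. The research team evaluates SAEs, the pharmacovigilance unit reviews forms and keeps a record of them, and annual safety reports are issued. Section 6.7 says only that a dedicated committee is not required, which is weaker than forbidding one. This stands: it would be wrong to infer that nobody looks at safety. What is missing is any comparison by arm, and 12.6 depends on one.

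Three stronger readings are tempting, and the documents do not support them.

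- *Related events cannot occur in the control arm.* Section 6.4.2 gives controls the information component of the intervention, and the written definition of a related event refers to the antihypertensive drug, which can apply in both arms. The supportable statement is that the quantity is undefined, and near zero in controls on one plain reading.
- *The protocol concedes that a difference in SAEs is undetectable.* That remark in section 10 covers the tertiary combined endpoints. SAEs as defined in section 10 include any hospitalisation, and no overall SAE rate is given.
- *Repeated 5% testing would greatly inflate false stops.* With Fisher's test, 229 per arm and an equal true rate of 3%, two to four evenly spaced looks give a simulated false-signal chance of roughly 3% to 4.5%; at 1.5% it is about 2%. At these rates the test is conservative enough that the risk stays below 5%.

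It is also fair to say that the test and level may sit in an analysis plan not shown here, and that Annex 1 already asks for the treatment assigned at randomisation. Neither point removes the conflict.

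**Conclusion.** The conflict is real and rests on the text alone: 12.6 requires an action that depends on an analysis which 6.7 says will not be done. It must be corrected. The second part also holds. As written, the events to be compared are not defined well enough for a between-arm test, because drug-relatedness and intervention-relatedness are different quantities and only the first has criteria.

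The size depends on the reading: 6 v 0 if control events are nil, or 18 v 7 if control events run at about 3%, with about 27% power for a doubling from 3% to 6%. These figures assume a two-sided 5% Fisher test on all 229 patients per arm, and the 3% is borrowed from the combined endpoints. They illustrate how differently the sentence could operate and do not predict SAE counts. The primary outcome, its sample size and its analysis are unaffected unless an unscheduled test is actually run.

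**What to change.** Reconcile sections 6.7 and 12.6 in one of two ways.

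- **Keep a comparison.** State in both sections that safety will be compared by arm, who does it, at which of the already planned annual safety reports, at what level fixed in advance, and on which events. Define those events so that they are ascertained in the same way in both arms.
- **Drop the comparison.** Replace 12.6 with a description of the non-comparative review that is actually intended, so that it agrees with 6.7.

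In either case, define relation to the intervention separately from relation to the antihypertensive drug, and give it its own entry in the pharmacovigilance record. Which stopping criterion applies is for the sponsor to settle.

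The cost is protocol wording and, if the comparison is kept, one table by arm in the existing annual report. The correction does not in itself call for a new committee.

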## **13. FUNDING AND INSURANCE**

### **13.1 Funding**

Granted concurrent research aid from the National R+D+i Plan (FIS Projects) in its last call (PI16/02130).

